### Sample size determination and sampling technique

The sample size for the study is determined by considering the longitudinal (repeated measure from each subject over time) and clustered (study subjects nested in health facilities (clusters)) nature of the study. First, the sample size is determined by considering the longitudinal nature of the study using the formula for comparing two means [12] with the aim of detecting a 10% improvement from the mean + SD value of 15.8 + 4.4 for fine motor score of developmental domain which was obtained from similar study conducted in Ethiopia [6]. Four measurements are planned in the study. These include before the intervention when the child will be transferred from Phase I to the Transition Phase (baseline measurement), upon discharge from the SC of the health facilities and at three and 6 months. Thus, the number of time points of measurement taken from each study subjects; t = 4, type one error = 0.05, power = 90%, smallest meaningful difference d = 10% and the assumed correlation (r) of the repeated measures *r* = 0.02. Consequently, a sample of 44 children with the diagnosis of SAM satisfying the admission criteria to the SC per group will be required under individual randomization. The calculated sample size under individual randomization was further adjusted to account for the effect of clustering with an assumed Intracluster Correlation Coefficient (ICC) ρ = 0.05. Since this study is a trial with a fixed number of equal-sized clusters (k) the required sample size per group is obtained using the formula proposed by Hemming [13]. After considering, 20% of the calculated sample size for the potential dropout, 68 children will be required for each of the study groups. The corresponding number of individuals in each of the health facilities (clusters) is determined using the formula [13]. Accordingly, approximately eight study subjects from each of the study health facilities (clusters) will be required making the final sample 72 children with SAM for each of the study groups. Thus, 144 children with SAM age 6–59 months satisfying the inpatient admission criteria will be recruited and included in the two study groups. Based on the recommendation of Hemming [13] this trial is feasible since the number of clusters k = 9 per group is greater than the product of the number of individuals required under individual randomization (*n* = 44) and ICC (ρ = 0.05). Based on the report of the Silti Zone Health Office, the achievement of the target sample of children with SAM is feasible during the recruitment period.

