
### Randomization

There are a total of, *K* **=** 18 study health facilities (clusters), k = 9 clusters will be used in each of the two intervention groups. The interventions will be allocated randomly to the study health facilities (clusters) by using a table of random numbers by an independent randomization manager who will not know anything about neither the interventions nor the health facilities (clusters). The allocation code will be concealed from the randomization manager to either of study groups using sealed opaque envelopes.

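### The stated 90% power counts the pre-intervention visit as one of four outcome measurements and rests on an unjustified repeated-measures correlation of 0.02; without the baseline visit, the protocol's own inputs give about 83%

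*Protocol article*

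**What the plan says.** All inputs are in the protocol article, under Sample size determination and sampling technique, unless noted.

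- The target is "detecting a 10% improvement from the mean + SD value of 15.8 + 4.4 for fine motor score", that is 1.58 points with SD 4.4, at 90% power and "type one error = 0.05".
- The repeated-measures part uses "the number of time points of measurement taken from each study subjects; t = 4". The same paragraph lists the four visits, and the first is pre-intervention: "These include before the intervention when the child will be transferred from Phase I to the Transition Phase (baseline measurement". The others are at discharge, 3 months and 6 months. Outcome measurement and tools gives the same schedule.
- "the assumed correlation (r) of the repeated measures" is set at 0.02, with no source or reason.
- Clustering enters through "an assumed Intracluster Correlation Coefficient (ICC) ρ = 0.05" and a formula for a fixed number of clusters. The Randomization section confirms that "k = 9 clusters will be used in each of the two intervention groups".
- The results are 44 per group under individual randomization, 68 after clustering and 20% for dropout, and 72 after rounding to eight children per facility (144 in all).

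**The concern.** Sizing on the mean of t repeated measurements is legitimate when every one of them estimates the intervention effect. Here one of the four is taken before the intervention starts. It can sharpen the comparison as a covariate, but it is not a further reading of the effect.

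The second input pulls the same way. In this formula the saving from repeated visits is greatest when r is near zero, so 0.02 is close to the most favourable non-negative value available. It implies that a child's fine motor score says almost nothing about the same child's score weeks or months later, and the protocol offers no evidence for that.

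The stake is how the result is read. If the trial finds no difference, readers will take it as a 90%-powered negative for a 10% effect, and the stated calculation does not support that.

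**Working it through.** **Inputs from the protocol.** Difference d = 0.10 × 15.8 = 1.58; SD 4.4; type I error 0.05; power 90%; t = 4; r = 0.02; ICC 0.05; 9 clusters per group; 72 enrolled per group; 20% dropout. Sidedness is not stated. Two-sided is assumed, because it reproduces 44 and a one-sided test would give 36.

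**Reproducing the plan.**

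1. Single visit: 2 × (1.96 + 1.2816)² × (4.4/1.58)² = 163.0 per group.
2. Repeated-measures factor (1 + (t − 1)r)/t = (1 + 3 × 0.02)/4 = 0.265; 163.0 × 0.265 = 43.2, so 44.
3. Fixed number of clusters, n(1 − ICC)k/(k − n × ICC): 44 × 0.95 × 9/(9 − 2.2) = 55.3, so 56.
4. Dropout: 56 × 1.2 = 67.2, so 68. Then 68/9 = 7.6, so 8 per facility and 72 per group.

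Every printed figure matches. The arithmetic is sound; the question is what was put into step 2.

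**Same inputs, three post-baseline visits.**

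1. Factor (1 + 2 × 0.02)/3 = 0.347; 163.0 × 0.347 = 56.5, so 57.
2. 57 × 0.95 × 9/(9 − 2.85) = 79.2 completers per group. Rounding up to 80 and multiplying by 1.2 gives 96 enrolled.
3. The feasibility condition still passes: 9 > 57 × 0.05 = 2.85.

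**Power with 72 enrolled.** With N evaluable children per group, the design effect is 1 + (N/9 − 1) × 0.05 and the standard error is 4.4 × √(factor × design effect × 2/N).

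- After 20% dropout: N = 57.6, design effect 1.27, SE = 4.4 × √(0.347 × 1.27 × 2/57.6) = 0.544. Then 1.58/0.544 = 2.90, and 2.90 − 1.96 = 0.94, so power is 83%.
- With no dropout: N = 72, design effect 1.35, SE = 0.502, power 88%.
- With a t-test on 16 df (18 clusters): 78% and 84%.
- With baseline as a covariate the factor becomes (1 + 2r)/3 − r² (equal correlation between all visits). At r = 0.02 this is 0.346, so power is unchanged.
- For comparison, the plan's factor of 0.265 with N = 57.6 gives 91% (88% on 16 df).

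**Sensitivity to r.** Even if all four visits are counted, 90% after dropout holds only up to r of about 0.04 (about 0.10 with no dropout).

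Illustration for the baseline-adjusted mean of three post-baseline visits, N = 57.6. Here r is an assumption, because the protocol gives no other value:

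| r | factor (1 + 2r)/3 − r² | z-based power | 16-df power |
|---|---|---|---|
| 0.02 | 0.346 | 83% | 78% |
| 0.3 | 0.443 | 73% | 67% |
| 0.5 | 0.417 | 75% | 70% |
| 0.7 | 0.310 | 87% | 82% |
| 0.8 | 0.227 | 95% | 92% |

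On the z basis the curve reaches 90% at r of about 0.74 (about 0.68 with no dropout).

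**The case against.** The strongest reply is that the trial may still have 90% power. Data management and analysis plans a generalized linear mixed model on the repeated measurements, controlling for other factors. How baseline enters that model is properly left to a fuller document. The outcome is a sum of items in children aged 6 to 59 months, so differences between children that go with age should persist across visits, and r could be high. At about 0.74 or above, a baseline-adjusted analysis reaches 90% after dropout. This stands. A reader might infer that the design cannot deliver 90%, and the documents do not support that. However, the rescue needs an r very different from the stated 0.02 and a calculation that the protocol does not present, so it does not defend the claim as written.

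A reader might also infer that power is far below 90%, for example from the 65%, 55% and 48% that an unadjusted three-visit mean would have at r = 0.3, 0.5 and 0.7. The protocol does not commit to an unadjusted analysis, so those figures should not be held against it.

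A third tempting inference is that r = 0.02 is impossible because it lies below the ICC of 0.05, given that two visits of one child share the facility as well as the child. That holds only if both values describe a single-visit score and the facility effect is stable. The protocol applies the ICC to 44, which is already the size for an averaged score. Read that way, the facility share at a single visit is 0.05 × 0.265 = 0.013, below 0.02, and nothing conflicts. The text does not settle which reading is meant, so the point is not relied on here.

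**Conclusion.** The stated calculation does not support 90% power for a 10% difference. Correcting only the count of visits, and keeping the protocol's own r, SD, ICC, difference and dropout, lowers power to about 83% (78% on 16 df), or 88% (84%) if no child is lost. This needs no outside figure. It rests on a two-sided test and on the ICC applying to the averaged score, as in the protocol's own chain.

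The value r = 0.02 is a separate weakness: it is unjustified, it is favourable in this formula, and the 90% is sensitive to it. What the true r would do to power cannot be settled from the document. Over assumed values of 0.3 to 0.8, baseline-adjusted power after dropout runs from 73% to 95% on the z basis and from 67% to 92% on 16 df. The fault lies in the inputs and their justification, not in the arithmetic or in the feasibility of the design.

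**What to change.** In the sample-size section:

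- Remove the statement that this calculation gives 90% power for a 10% difference.
- Recompute with t = 3 post-baseline visits and baseline as a covariate, and name that analysis as the one the power refers to.
- Give the source or reasoning for r.
- Report power for the fixed 144 children over a wide range of r, including values above 0.7, with 16-df quantiles. A single restated power tied to one unsourced r would repeat the present problem.

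The cost is a rewritten paragraph and, for most values of r, a less favourable stated power. No extra children, visits or facilities are needed, and trial conduct does not change.

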The model is appropriate for the present study considering the correlated nature of the repeated measurements from each study subject and from the hierarchical structure of data that study subjects nested in health facilities (clusters). In all the analysis variables with a *p*-value < 0.05 will be considered statistically significant.

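### The ICC of 0.05 is applied to a sample size already cut about 3.7-fold for four visits; if it is an ordinary single-score ICC and facility differences last, 9 facilities of 8 children per arm give about 73% power, not 90%

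*Protocol article*

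**What the plan says.** All of this stands in the protocol article under Sample size determination and sampling technique, except where noted.

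- The target is "detecting a 10% improvement from the mean + SD value of 15.8 + 4.4 for fine motor score", with "type one error = 0.05, power = 90%, smallest meaningful difference d = 10"%.
- The repeated-measures step uses "the number of time points of measurement taken from each study subjects; t = 4" and "the assumed correlation (r) of the repeated measures *r* = 0.02", and arrives at 44 children per group under individual randomization.
- That figure is then "adjusted to account for the effect of clustering with an assumed Intracluster Correlation Coefficient (ICC) ρ = 0.05", using a formula for a fixed number of equal-sized clusters with 9 per arm. With 20% for dropout this gives 68 per group, rounded to 8 per facility and 72 per group.
- Feasibility is declared because "this trial is feasible since the number of clusters k = 9 per group is greater than the product" of 44 and 0.05.
- Data management and analysis justifies the mixed model by the repeated measurements and "from the hierarchical structure of data that study subjects nested in health facilities (clusters").

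The text does not say whether the ICC refers to one score or to the average of a child's four scores, and gives no source for it.

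**The concern.** Averaging a child's visits reduces that child's visit-to-visit variation. It does not reduce a difference between facilities that is shared by all their children at every visit. The 44 is the size needed for a four-visit mean, whose variance is only 0.265 of a single score's. Attaching 0.05 to it therefore scales the facility variance down by the same factor as the visit noise.

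The document gives reasons to expect lasting facility differences. Study area and design describes caregivers living and eating together through an extended stay, and Personnel for the study assigns one play guide to each facility, who continues through six months of home visits.

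At stake are the stated 90% power and the impression that 9 facilities per arm leave ample room. A null result would be read as coming from a trial with 90% power when the design may be considerably weaker.

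**Working it through.** **Inputs** (all from the sample size section): difference 10% of 15.8 = 1.58; SD 4.4, so σ² = 19.36; alpha 0.05, taken as two-sided because that reproduces 44; power 90%; t = 4; r = 0.02; ρ = 0.05; k = 9 per arm; dropout 20%.

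**Reproducing the plan**
- Single score, individual randomization: 2(1.960 + 1.282)² × 19.36 / 1.58² = 163 per group.
- Four visits: 163 × (1 + 3×0.02)/4 = 163 × 0.265 = 43.2, printed as 44 (163/44 = 3.7-fold).
- Clustering: 44 × 9 × 0.95 / (9 − 44×0.05) = 376.2 / 6.8 = 55.3, rounded up to 56 per group.
- Dropout: 56 × 1.2 = 67.2, printed as 68. Then 68/9 = 7.6, rounded to 8, giving 72 per group.
- Feasibility product: 44 × 0.05 = 2.2.

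The chain reproduces, so the order of the steps is clear. After 20% loss, 72 × 0.8 = 57.6 children per arm remain, or m = 6.4 per facility.

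**What the clustering step implies.** The facility variance it uses is 0.05 × 0.265σ² = 0.013σ². An ICC of 0.05 on a single score means 0.05σ². If that variance persists over visits, the ICC belonging with the four-visit mean is 0.05/0.265 = 0.19 (0.05/0.2875 = 0.17 at r = 0.05).

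**Coherence of r and ρ.** Two scores of one child share a facility. With a lasting facility effect and ρ = 0.05 on a single score, they must correlate at least 0.05, so r = 0.02 is not possible. If r = 0.02 is kept, the facility effect can correlate across visits at most 0.02/0.05 = 0.4.

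**Power.** With V = (1 + 3r)/4 and F the facility variance of the four-visit mean (both in units of σ²),

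Var(difference) = (2 × 19.36/9) × [F + (V − F)/m].

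The plan's method sets F = 0.05V. A lasting single-score effect sets F = 0.05.

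| Case | m | Power, normal | Power, t (16 df) |
|---|---|---|---|
| Plan's method, r = 0.02 | 6.4 | 91% | 88% |
| Plan's method, r = 0.05 | 6.4 | 89% | not computed |
| Lasting effect, r = 0.05 | 6.4 | 73% | 68% |
| Lasting effect, r = 0.05 | 8 | 77% | 72% |
| Partly lasting (autocorrelation 0.4), r = 0.02 | 6.4 | 85% | 80% |

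Worked lines at m = 6.4:
- Lasting, r = 0.05: 4.302 × [0.05 + 0.2375/6.4] = 0.375; SE 0.612; 1.58/0.612 − 1.96 = 0.62; power 73%.
- Plan's method, r = 0.05: 4.302 × 0.2875 × [0.05 + 0.95/6.4] = 0.245; SE 0.495; power 89%.
- Autocorrelation 0.4: F = 0.05 × (1 + 3×0.4)/4 = 0.0275; 4.302 × [0.0275 + 0.2375/6.4] = 0.278; SE 0.527; power 85%.

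Weaker persistence raises the last figure: 88% at autocorrelation 0.2 and 92% at zero (normal), the latter meaning facility effects that are unrelated from one visit to the next.

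**Feasibility on the single-score scale.** The product is 163 × 0.05 = 8.15, whatever the number of visits, so 9 > 8.15 passes with 0.85 to spare. At r = 0.05, 90% power by the normal test would need 163 × 0.2375 / (9 − 8.15), about 45 children per facility. With unlimited children per facility, power tops out at 92.6% (normal) or 89.2% (t, 16 df).

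**Dependence on r** (normal test, m = 6.4, plan's method against lasting effect): 89% against 73% at r = 0.05; 70% against 61% at r = 0.3; 58% against 53% at r = 0.5; 49% against 47% at r = 0.7.

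**The case against.** The strongest reply is that the ICC's scale is not stated. If 0.05 is the ICC of the four-visit mean, it is applied exactly where it belongs, the arithmetic is consistent, and power after dropout is about 91%. On that reading the single-score ICC is 0.013, below r = 0.02, and the two inputs do not conflict. This stands, and it is why the conclusion is conditional. Nothing in the section supports that reading, however, and the value it implies is neither printed nor justified. Nor does the article say that facility effects are constant over visits; the planned mixed model allows for nesting without settling that.

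A second reply is that 73% does not use the printed r. That is right: it uses 0.05, the lowest value a lasting effect permits. The like-for-like comparison is 73% against 89%, not against 91%.

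Third, the figure of 45 children per facility rests on a denominator of 0.85 and is fragile. The same formula gives 16 at ρ = 0.04 and 10 at ρ = 0.03. It shows how near the limit the design lies and is not a recruitment target.

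Two stronger readings are tempting and not supported. A reader might infer that the feasibility check fails; it does not, since 9 exceeds 8.15, and only the margin is misstated. A reader might also infer that the error is present whatever the number of visits or the value of r. It disappears with one visit or with r = 1, and the gap between the methods is small when r is high.

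**Conclusion.** The point holds conditionally. The plan's method treats facility differences as averaging out over visits, and the stated power is recovered only if 0.05 is the ICC of the visit mean (about 0.013 on a single score) or if facility effects hardly persist from visit to visit. For an ordinary single-score ICC of 0.05 with lasting facility differences, and r at 0.05, the design has about 73% power (68% by t) after dropout and 77% (72%) with no loss. If r = 0.02 is kept, persistence is at most partial and power is as low as 85% (80%). These figures retain the plan's other favourable choices: a difference of 1.58, SD 4.4, and all four visits, baseline included, carrying the effect. It cannot be said that the 90% is wrong on every reading of the inputs, because the scale of the ICC is undefined.

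**What to change.** In the sample size section, state whether ρ = 0.05 applies to a single score or to the four-visit mean.

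- **Single score:** keep the facility variance at ρσ² and divide only the within-facility part by the number of visits. Use an r not below ρ. Print the feasibility comparison as 8.15 against 9. Keep 9 facilities of 8 children per arm, and restate the power as about 73% (68% by t) after dropout. Give the range up to 85% (80% by t) for a facility effect with autocorrelation 0.4, and name the persistence assumed.
- **Four-visit mean:** say so, and print and justify the implied single-score ICC of about 0.013. The printed r = 0.02 then needs no change on this account.

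The cost is recalculating and rewording one paragraph, with no change to enrolment. The downside on the first option is a less favourable stated power.

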
### Randomization

There are a total of, *K* **=** 18 study health facilities (clusters), k = 9 clusters will be used in each of the two intervention groups. The interventions will be allocated randomly to the study health facilities (clusters) by using a table of random numbers by an independent randomization manager who will not know anything about neither the interventions nor the health facilities (clusters). The allocation code will be concealed from the randomization manager to either of study groups using sealed opaque envelopes.

### Personnel for the study

Health workers who will be recruited from the SC of each of the health facilities will take the responsibility for the recruitment; follow up of children during the SC admission period, for supporting the intervention workers/play guides and for the collection of enrollment and other data. Depending on the caseload in the SC of the health facility, one or two health workers will be included in the study team from each of the health facilities.

For each of the health facilities, one young female intervention worker/ play guide who have completed at least grade 10 will be recruited from the local community considering their child-friendliness. In the intervention health facilities, the intervention workers/ play guides will assume the responsibility of facilitating the stimulation intervention during the inpatient care and for the period of 6 months after discharge through a home visit. They will also provide health education, conduct home-based follow up, collect follow up data, participate in the preparation of suitable toys from locally available materials, help mothers/ caregivers and other family members, and equip them with the essential skills for the implementation of the intervention. For each of the control health facilities, the intervention worker will only be responsible for providing health education, conducting home-based follow-up, and collection follow-up data. A separate mobile team of testers/ outcome assessors will be recruited considering their academic background and previous experience to collect anthropometric data and administer developmental tests. They will be unaware (Blind) to the allocation status of the children and the health facilities to avoid measurement bias.

Experienced supervisors will be recruited to oversee the activities of the health workers, the team of testers/ outcome assessors and the intervention workers. The field-level project coordinator under the direct guidance of the principal investigator will be responsible for the overall coordination and follow up.

### Training of the study team

Intensive training will be given for the study personnel by a team of senior trainers. Separate training will be provided for each of the study teams considering the allocation status of their health facilities, their role in the study and their professional experience. For the intervention health facilities, health workers will be trained on the basis of psychosocial stimulation and the study procedures including recruitment and data collection procedures, facilitation of psychosocial stimulation, and facility-level follow up procedures. The training of the intervention workers/play guides will focus on the basics of childcare, child growth, and development, about the communication methods and other intervention-related issues such as the study procedures, the facilitation of the stimulation intervention and follow up procedures. For the control health facilities, the training of both the health workers and intervention workers/ play guides will not include the stimulation intervention related topics. The measurement team will also be trained on the standards of anthropometric measurement and administration of development tests. In all the training sessions, the trainees will go out to the field to practice the practical components of the training.

